**Table 1 T1:**
[figure not shown]
Sample allocation (case group).

A total of 28 patients will be recruited into the control group (0.5 time the sample size of the patient group) for comparison. The proportionate allocation results of the 28 control patients will be selected for frequency matching for each stratum, using the same ratio as in the stroke patient group. (Table 2)

**Table 2 T2:**
[figure not shown]
Sample allocation (control group).

#### Randomization and blinding

2.4.5

This clinical study was designed as a case-control study. Therefore, consideration of the method of randomization and blinding is not needed.

#### Collection of demographic and lifestyle information

2.4.6

The medical history of the participants, including their current medication status and surgical history, the presence of other diseases, and the results of their electrocardiography and pregnancy tests, will be recorded at baseline. Lifestyle factors including exercise, smoking, caffeine intake, and alcohol consumption will also be documented. In addition, the patients’ hypertension, height, weight, and other demographic information will be obtained.

### Data collection

2.5

The data will be collected through a participant survey and through investigator measurements at baseline (on visit 1) and at specified follow-up times (on visits 2 to 7). (Table 3)

**Table 3 T3:**
[figure not shown]
Schedule for study procedure.

### Devices and measurement techniques

2.6

#### Pulse tonometric device (KIOM-PAS)

2.6.1

The KIOM-PAS will be acquired with a pulse tonometric device developed at the Korean Institute of Oriental Medicine in Daejeon, Korea. This device consists of a main body with an arm holder and a sensing body attached to a mobile actuator. A pulse detection sensor composed of 7 piezoresistive unit sensors within 9×9 mm^2^ is located at the actuator tip. A previous study we conducted found that the radial artery was more superficial at Gwan (Guan: prominent bone) than Chon (Cun) and Cheok (Chi).^[9]^ Therefore, in this study, the operator will measure the pulse signals at Gwan.

#### Physiological data acquisition system (Biopac module)

2.6.2

The physiological data will be obtained with a Biopac MP150 (Biopac module, Biopac Systems Inc., USA). The heart rate (HRV) signal will be obtained with an ECG100C. The respiration (RSP) signal will be obtained with a SKT100C. The mean AUC of the photoplethysmogram (MAUGppg) signal will be obtained with a PPG100C.

#### Blood viscosity measurement (VISCORE-300)

2.6.3

Viscore-300 is a device designed to measure the viscosity with a V-Chip. This chip enables measurement from a small quantity of fluid (0.5cc) and consists of a lab-on-a-chip, a syringe, and a mounting case. The lab-on-a-chip is fitted with 150 microfluidic channels (50 μm), allowing the viscosity to be measured with high precision and replication. The viscosity will be determined by measuring the relative viscosity between the reference fluid and the sample fluid.

### Outcome measures

2.7

#### Primary outcome

2.7.1

Radial augmentation index (rAIx) The radial augmentation index (rAIx) measures the vascular compliance and stiffness of the radial arterial vessel walls, that is, the degree of variation in the magnitude of the pulse wave by the reflected wave. The radial augmentation will be calculated from the radial wave pulse as follows: (second peak SBP (SBP2) DBP)/(first peak SBP_DBP)_100,13, as shown in Figure 1.

**Figure 1 F1:**
[figure not shown]
Single pulse waveform at radial artery as a function of time.

#### Secondary outcomes

2.7.2

(1) Spectrum energy 0–10 Hz (SE0–10 Hz)/Spectrum energy 10–30 Hz (SE10–30 Hz)

The power spectral density of 60-second pulse waves will be obtained under constant hold-down pressure. The width values of the power spectral densities within 0–10 Hz and 10–30 Hz variations will be calculated.

(2) Pulse power index (PPI)

The pulse waveform initiation point and peak of the pulse waves will be extracted, and the largest peak amplitude (at optimal hold-down pressure) will be defined as the pulse power index, as shown in Figure 2.

**Figure 2 F2:**
[figure not shown]
Pulse waveform extraction as a function of sensor displacement from the skin contact point of the measurement sensor.

(3) Heart rate variability (HRV)

The heart beat intervals between the R peaks of the electrocardiograms will be Fourier-transformed to obtain the frequency domain power spectrum of the heart rate variability. LF (0∼0.15 Hz) area mainly reflects the activity of the sympathetic nervous system and HF (0.15∼0.4 Hz) area reflects the activity of the parasympathetic nervous system. Quantitative evaluation of sympathetic and parasympathetic activity is available (Fig. 3).

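### The LF band of heart rate variability has no positive lower limit, so slow fluctuation and drift are counted as LF and would be read as sympathetic activity

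*Protocol article*

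**What the plan says.** Heart rate variability is the third secondary outcome in section 2.7.2 of the protocol article. The processing is described in one sentence: "The heart beat intervals between the R peaks of the electrocardiograms will be Fourier-transformed" in order "to obtain the frequency domain power spectrum of the heart rate variability". Two areas are then taken from the spectrum and interpreted:

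- Low frequency: "LF (0∼0.15 Hz) area mainly reflects the activity of the sympathetic nervous system".
- High frequency: "HF (0.15∼0.4 Hz) area reflects the activity of the parasympathetic nervous system".

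The item closes with the claim "Quantitative evaluation of sympathetic and parasympathetic activity is available". The article gives no lower limit for LF other than 0, no separate band for slower variation, and no record length for this measurement. Figure 3, which shows the spectrum, is not available in the text reviewed.

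**The concern.** The two bands are not built alike. HF has a positive lower limit. LF does not, so it collects everything slower than 0.15 Hz: the oscillation it is meant to capture, any slower wave, and any trend while the participant settles or the signal wanders.

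The whole area is then given one physiological meaning. The study compares patients with matched controls (section 2.1) and follows participants from visit 1 to visit 7 (section 2.5). If groups or visits differ only in slow drift, LF will differ, and the protocol's own wording would have that read as a difference in sympathetic activity.

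This is a point about a numeric definition that the article states, not about a detail it leaves out.

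**Working it through.** There is no computed figure to reproduce, because the point concerns a band definition. The check is what an area from 0 to 0.15 Hz contains.

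**From the article:** LF 0 to 0.15 Hz; HF 0.15 to 0.4 Hz; Fourier transform of R-R intervals.

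**Assumed, not in the article:** mean R-R 850 ms; resampling at 4 Hz; one component at 0.10 Hz and one at 0.25 Hz, each with SD 20 ms; one slow component between 0.003 and 0.04 Hz with SD s = 0, 10, 20 or 30 ms; records of 60 s and 300 s; 400 simulated series per setting.

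**Step 1, by hand.** The power of a component is its SD squared. The 0.10 Hz component has 20² = 400 ms². With the mean removed, the area from 0 to 0.15 Hz should be close to 400 + s²: 400, 500, 800 and 1,300 ms².

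**Step 2, by simulation** (mean areas in ms²; the true 0.10 Hz power is 400 throughout):

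| Record | s (ms) | 0–0.15 Hz, mean removed | 0–0.15 Hz, linearly detrended | 0.04–0.15 Hz | HF |
|---|---|---|---|---|---|
| 300 s | 0 | 400 | 400 | 400 | 400 |
| 300 s | 10 | 500 | 498 | 407 | 400 |
| 300 s | 20 | 797 | 790 | 422 | 401 |
| 300 s | 30 | 1,296 | 1,276 | 445 | 402 |
| 60 s | 0 | 400 | 397 | 400 | 400 |
| 60 s | 10 | 484 | 462 | 407 | 401 |
| 60 s | 20 | 749 | 664 | 422 | 404 |
| 60 s | 30 | 1,163 | 989 | 448 | 408 |

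The inflation of LF after mean removal runs from 400/400 = 1.0 to 1,296/400 = 3.2 for the 300 s record, and from 1.0 to 1,163/400 = 2.9 for the 60 s record. After linear detrending the worst cases are 1,276/400 = 3.2 and 989/400 = 2.5. With a lower limit of 0.04 Hz the worst case is 448/400 = 1.12, the excess being leakage from the slow component. HF moves by at most 408/400 = 1.02.

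**Step 3, straight-line drift.** A linear drift of D ms over the record adds a variance of D²/12: 75 ms² for 30 ms and 300 ms² for 60 ms. Detrending removes this part. It does not remove a slow wave, which is why it helps so little in the table.

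**Step 4, what a comparison would show.** Take two groups with the same 0.10 Hz power of 400 ms² and slow SDs of 10 and 20 ms (300 s, mean removed). Their LF areas are 500 and 797 ms², a ratio of 797/500 = 1.59, with no difference in the oscillation of interest.

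**Step 5, the mean.** If the series were transformed without centring, the zero-frequency term would add 850² = 722,500 ms² and LF would be about 723,000 ms². This case is conditional and is not used for the size of the effect.

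**The case against.** Five things can be said for the plan.

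- **The mean is probably removed.** A reader might infer that LF here is essentially a measure of mean heart rate, inflated thousands of times. The documents do not support that. The article speaks of a spectrum of variability, which most naturally means variation about the mean, and an article may leave centring and detrending to the full protocol. This stands, and the silence on preprocessing is no finding. It answers only the part about the mean, because the inflation in the table is present after centring.
- **The band still contains what it should.** A reader might infer that LF fails to measure low-frequency variability at all. That is too strong. With no slow component the stated band returns exactly 400 ms². The fault is mixing, and the article itself says only that LF mainly reflects sympathetic activity.
- **No LF/HF ratio is named.** A distorted ratio is therefore not a consequence for any listed outcome. This stands. What remains is that two areas presented side by side are exposed unequally.
- **The zero may be a misprint.** This cannot be excluded, since Figure 3 might mark the edges. Even so, the published definition would then differ from the one applied and would need correcting.
- **The size rests on assumptions.** The amplitudes, mean R-R and record lengths are not in the article. This stands, and it is why the result is given as a range that includes no effect.

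**Conclusion.** The point holds in a limited form. As printed, the LF band has no positive lower limit, so slow fluctuation and drift count as LF and would be interpreted as sympathetic activity, while HF is largely spared. That such variation is counted follows from the definition alone. How much it matters does not: under assumed slow components with SD up to 30 ms, LF after mean removal is inflated from not at all to about threefold, and linear detrending alone does not cure this. The mean R-R interval enters only if the series is not centred, which the article neither states nor suggests.

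The reach is small. This is one of 17 listed secondary outcomes. The primary outcome, the radial augmentation index, and the sample size do not depend on it.

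**What to change.** - State a lower limit for LF above 0 Hz. An edge of 0.04 Hz was used in the check above; it is not in the article, so the sponsor should confirm it or name another.
- State that the limit is applied to R-R series that have been mean-centred and detrended.
- Report power below the limit separately, or not at all, and do not label it sympathetic.
- If 0 is a misprint, correct it so that the published definition matches the one applied.

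The cost is one number and one sentence on processing. The R-R data need no new recording and can be re-banded at any time. The limit is best fixed before the outcome is analysed.

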**Figure 3 F3:**
[figure not shown]
Power spectral density (PSD) of HRV signal obtained from electrocardiogram.

(4) Respiration (RSP)

A fast-response surface temperature thermistor will be attached to the participants’ philtrum region to measure the temperature changes as they inspire and exhale through their nose. The respiration rates will be measured using the flows of the temperature change signals (Fig. 4).

**Figure 4 F4:**
[figure not shown]
Respiration waves as measured by thermistor according to measurement time.

(5) Mean area under photoplethysmogram curve (MAUCppg)

The MAUCppg measuring method estimates the state of heartbeat activities using the optical characteristics of in vivo tissues to capture the changes in blood flow rates and blood vessel volumes caused by the dilatation and contraction of the heart. The mean PPG waveforms will be measured from the starting point to the end point, and the area below the mean waveform curve will be drawn (Fig. 5).

**Figure 5 F5:**
[figure not shown]
Pulse PPG waveform measured at patient's fingertip as a function of time.

(6) Brachial ankle pulse wave velocity (BaPWV).

The brachial-ankle pulse wave velocity (baPWV) is a unique measure of the systemic arterial stiffness. It is assessed through brachial and tibial arterial wave analyses.^[10]^

(7) Ankle-brachial index (ABI)

The ankle-brachial pressure index (ABPI)-or ankle-brachial index (ABI)-is the ratio of the blood pressure at the ankle to the blood pressure in the upper arm (brachium). Lower blood pressure in the leg than in the arm is an indication of blocked arteries due to peripheral artery disease (PAD). The ABPI is calculated by dividing the systolic blood pressure at the ankle by the systolic blood pressure in the arm:

ABI = SysBPLeg/SysBPArm,

where SysBPLeg indicates the systolic blood pressure in the leg and SysBPArm indicates the systolic blood pressure in the arm.

(8) Surface temperature on hand palms

To investigate the changes in stroke patients’ temperature over the course of the treatment, the temperature will be measured at the center of both palms 3 times. The mean temperature will be used in the analysis.

(9) Body composition analysis

To investigate the correlation between the body composition measurements and the changes in the radial pulse over the course of stroke treatment, the soft lean mass (SLM), total body water (TBW), and body fat mass (BFM) will be measured using Inbody S-10 (InBody, South Korea).

(10) Assessment of walking ability

Variables including the cadence, speed, stride length, and symmetry index will be measured using the G-Walk (BTS S.P.A, Italia, Seoul receiver 12–191) to assess the improvement in the walking ability over the course of the stroke treatment.

(11) Plasma inflammatory index

The plasma high-sensitivity C-reactive protein (hs-CRP) level will be measured.

(12) Thrombosis-related indices

The plasma levels of factors associated with thrombosis/hemostasis (the von Willebrand, D-dimer, and fibrinogen factors) will be measured.

(13) Plasma viscosity measurement

The following variables will be measured to assess the plasma viscosity: the systolic relative viscosity (SRV) – that is, the relative viscosity at which the shear rate (1/s) is 300-and the diastolic relative viscosity (DRV) – that is, the relative viscosity at which the shear rate (1/s) is 5.

(14) Manual muscle testing (MMT)

MMT is performed as a screening test and to identify the relationship with the radial artery pulse wave profile. It provides a baseline for therapy by assessing the potential muscle strength through the measurement of the resistance against gravity and against opposing forces in each muscle. It is used to explore the influence of muscle weakening on the activities of daily living and to select activities that can be performed within the patient's capacity, thus allowing to assess the treatment efficacy.

(15) Korean Version of National Institutes of Health Stroke Scale (K-NIHSS)

The Korean Version of National Institutes of Health Stroke Scale (K-NIHSS) is the most widely used tool for the absolute measurement of post-stroke disability. It comprises 14 categories that assess the cognitive level, gaze, field of vision, facial palsy, limb power, loss of mobility, sensation, language, dysarthria, neglect, and distal upper limb movement.

(16) Beck depression inventory (BDI)

The Beck depression inventory (BDI) is a self-reporting tool comprising 21 categories-including emotional, cognitive, causal, and physiological symptoms-that is used to assess depression in patients. Each of the 21 questions is scored between 0 and 3, for a total between 0 and 63. A score of 0–9 is considered normal, while 10–15 indicates mild depression, 16–23 indicates moderate depression, and 24–63 indicates severe depression.

(17) Blood stasis syndrome questionnaire (BSSQ)

The blood stasis syndrome questionnaire (BSSQ) was developed and validated by the Korea Institute of Oriental Medicine (KIOM) by integrating the Korean, Chinese, and Japanese blood stasis syndrome questionnaire (BSS) criteria in a community-based, multi-center trial.

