### Participants

2.4

A total of 84 participants will be enrolled in this matched case-control study. The cohort will comprise 56 patients with hemiplegia caused by stroke, and half the number of control patients matched by age, gender, and body mass index (BMI). The 56 participants with hemiplegia caused by stroke and the 28 healthy participants will be recruited through advertisements, and the 56 patients with stroke hemiplegia will be recruited among the outpatients or inpatients of the Wonkwang University Gwangju Hospital. Each participant will receive an explanation of the study procedure and will be asked to sign the consent form. The patients’ vital signs and relevant histories will be recorded.

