#### Exclusion criteria

2.4.2

- Case group(1)Patients diagnosed with a hemorrhagic stroke through CT or MRI scans.(2)Patients whose pulse waves cannot be easily measured due to malformation of their blood vessels around the wrist or to bone fractures, or patients who cannot comply with the test procedure for other reasons.(3)Patients with serious organic diseases (cardiac disorders or lung, liver, or kidney diseases), or a history of a central nervous system or psychiatric disorder or of taking psychoactive drugs.(4)Patients with neurological disorders other than strokes.(5)Patients with a SBP < 90 mmHg or > 220 mmHg, and/or a DBP < 40 mmHg or > 130 mmHg.(6)Patients with severe musculoskeletal diseases from injury or rheumatic diseases.(7)Pregnant or nursing women.(8)Patients with implanted cardiac pacemakers and electronic devices.(9)Patients who show skin trouble around the electrode attachment region or side effects during the electrode attachment.(10)Patients who cannot comply with the stroke clinical pathway (CP) provided by the treatment institution.(11)Patients with an unstable heartbeat.(12)Patients with a history of drug or alcohol abuse.(13)Patients who have participated in other clinical trials in the past 3 months.(14)Patients who have an abnormal reaction to traditional Korean medicine or acupuncture.(15)Patients considered inappropriate for the clinical study by the research head or staff.

- Control group(1)Subjects whose pulse waves cannot be easily measured due to malformation of their blood vessels around the wrist or to bone fractures, or subjects who cannot comply with the test procedure for other reasons.(2)Subjects with serious organic diseases (cardiac disorders or lung, liver, or kidney diseases), or a history of a central nervous system or psychiatric disorder or of taking psychoactive drugs.(3)Subjects with severe musculoskeletal diseases from injury or rheumatic diseases.(4)Subjects with a SBP < 90 mmHg or > 220 mmHg, and/or a DBP < 40 mmHg or > 130 mmHg.(5)Pregnant or nursing women.(6)Subjects with implanted cardiac pacemakers or electronic devices.(7)Subjects who show skin trouble around the electrode attachment region or side effects during the electrode attachment.(8)Subjects with an unstable heartbeat.(9)Subjects with a history of drug or alcohol abuse.(10)Subjects who have participated in other clinical tests in the past 3 months.(11)Subjects considered inappropriate for the clinical study by the research head or staff.

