#### Participant recruitment

2.4.3

The participants will be recruited through advertisements on hospital websites and on bulletin boards. They will be fully briefed on the study, including on the measuring methods and the procedures used. The subjects interested in participating will be guided through the informed consent process by the investigator on their first visit. Once their written consent is obtained, they will be screened using inclusion/exclusion criteria to determine their eligibility. If eligible, a physician will acquire the baseline data, and the clinical research coordinator will then schedule the study procedure. The participant recruitment will be stratified by age, gender, and BMI.

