### Statistical analysis

2.8

The software package R (version 3.0.1, “R & R” of the Statistics Department of the University of Auckland, Auckland, New Zealand) or STATA version 13.1 (StataCorp, College Station, TX, USA) will be used for the statistical analyses. To ensure sensitivity analyses, analyses of the primary and secondary outcomes will be conducted on the full analysis set (FAS) and per protocol set (PP). The last observation carried forward (LOCF) method will be used to impute the missing data.

Baseline characteristics will be presented using the t-test or Wilcoxon rank-sum test for continuous outcomes, and the chi-square test or Fisher's exact test for categorical outcomes. The differences in the intergroup comparisons of the means will be processed with the least squared mean (LSM) and the standard deviation, and the intragroup comparisons of the mean values will be analyzed with a repeated-measures ANOVA (RMANOVA) or a linear mixed-effects model analysis (LME). *P* < 0.05 will be considered statistically significant. The time point difference in contrast with the baseline will be examined with Dunnett's test.

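### baPWV is read as arterial stiffness and compared between groups and over visits, but the plan names no step to separate stiffness from blood pressure at measurement

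*Protocol article*

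**What the plan says.** - **Meaning given to baPWV.** Secondary outcomes (2.7.2), item 6: "The brachial-ankle pulse wave velocity (baPWV) is a unique measure of the systemic arterial stiffness". On method it adds only "It is assessed through brachial and tibial arterial wave analyses". It states no pressure condition or correction.
- **Entry limits.** Exclusion criteria (2.4.2) rule out, for cases, "Patients with a SBP < 90 mmHg or > 220 mmHg, and/or a DBP < 40 mmHg or > 130 mmHg", and apply the same limits to controls: "Subjects with a SBP < 90 mmHg or > 220 mmHg, and/or a DBP < 40 mmHg or > 130 mmHg".
- **Matching.** Participants (2.4), Participant recruitment (2.4.3) and Sample size (2.4.4) use three factors: "The participant recruitment will be stratified by age, gender, and BMI". Neither blood pressure nor hypertension is among them.
- **Analysis.** Statistical analysis (2.8): "The differences in the intergroup comparisons of the means will be processed with the least squared mean (LSM) and the standard deviation". Within-group comparisons use repeated-measures ANOVA or a linear mixed-effects model, with Dunnett's test against baseline. No covariate is named.
- **Pressure data.** Vital signs are recorded (2.4), as is hypertension (2.4.6: "hypertension, height, weight, and other demographic information will be obtained"). Arm systolic pressure is needed for the ankle-brachial index (2.7.2, item 7). No use of any of these in interpreting baPWV is stated.
- **Intended conclusions.** The Discussion lists differences and changes in blood vessel properties among the outcomes, with 6 months of follow-up.

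**The concern.** Pulse wave velocity responds to the distending pressure at the time of measurement as well as to the arterial wall. This is general physiology; the article does not state it. The between-group comparison sets people within 6 months of an ischemic stroke against people without a stroke diagnosis, whom the article calls healthy. These groups may well differ in pressure, and the three matching factors do not control that directly. Pressure in the cases may also change over follow-up.

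In either situation baPWV would move with no change in the vessel wall. Because the article equates baPWV with stiffness, the result would naturally be reported as a difference or improvement in arterial stiffness. At stake is the interpretation of one secondary outcome, in both the between-group and the over-time comparison.

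**Working it through.** **1. Group sizes, reproduced from the plan.** The article states 47 cases before drop-out and a 15% drop-out rate: 47 / 0.85 = 55.3, rounded up to 56. Controls are 0.5 × 56 = 28, and 56 + 28 = 84, as stated. These figures are not in dispute and serve only as inputs to step 4.

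**2. What the entry limits allow.** Taking mean pressure as DBP + (SBP − DBP)/3, the lowest admissible pair, 90/40, gives 40 + 50/3 = 56.7 mmHg. The highest, 220/130, gives 130 + 90/3 = 160 mmHg. These are extremes for individuals, the same in both groups. They show that the criteria do not restrict pressure tightly; they say nothing about a group difference.

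**3. Shift in baPWV per mmHg.** Assume PWV is proportional to exp(g·P/2), with g from 0.012 to 0.020 per mmHg. Neither the form nor g comes from the documents. The relative shift for a mean-pressure difference ΔP is exp(g·ΔP/2) − 1:

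| ΔP (mmHg) | g = 0.012 | g = 0.017 | g = 0.020 |
|---|---|---|---|
| 0 | 0% | 0% | 0% |
| 10 | 6.2% | 8.9% | 10.5% |
| 20 | 12.7% | 18.5% | 22.1% |

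**4. Effect on the test.** Let the true stiffness difference be zero, r the correlation of baPWV with systolic pressure, and d the group difference in systolic pressure in SD units. Both are assumed, and r is taken to run wholly from pressure to baPWV. The spurious baPWV difference is r·d SD. With 28 v 56, SE = √(1/28 + 1/56) = 0.231. The rejection rate at two-sided 0.05 is Φ(r·d/SE − 1.96) + Φ(−r·d/SE − 1.96). The last column repeats this after 15% drop-out, about 24 v 47:

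| r | d (SD) | Spurious difference (SD) | Rejection, 28 v 56 | Rejection, 24 v 47 |
|---|---|---|---|---|
| any | 0 | 0 | 5% | 5% |
| 0.3 | 0.5 | 0.15 | 10% | 9% |
| 0.5 | 0.5 | 0.25 | 19% | 17% |
| 0.7 | 0.5 | 0.35 | 33% | 29% |
| 0.5 | 1.0 | 0.50 | 58% | 51% |

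With equal pressures there is no bias. With a moderate pressure gap, the chance of reporting a stiffness difference that does not exist is roughly two to six times the nominal 5%.

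**The case against.** **The analysis plan may already adjust.** Least squares means come from a fitted model, and a condensed article need not list covariates. This stands. A reader might infer that the plan compares raw means or rules out adjustment; Section 2.8 supports neither. The point does not rest on a missing covariate list. It rests on three things the article does state: the unqualified stiffness reading, matching that leaves out pressure, and comparisons between groups and over visits.

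**The entry limits are identical in both groups.** This also stands. A reader might infer that the 90 to 220 mmHg range itself produces an imbalance. It permits one but does not create it.

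**The size is assumed.** Correct. The documents give no pressure difference, no correlation and no pressure-velocity relation, and the bias is zero if pressures are equal. A reader might infer that the baPWV result is certain to be biased; the documents do not show that.

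**The sentence on baPWV is descriptive, and the Background's stated use is correlation with blood viscosity to evaluate prognosis.** For prognosis, unadjusted baPWV is a legitimate quantity. But the Discussion also makes differences and changes in vessel properties an outcome, and for that reading pressure matters.

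**Adjustment is contestable.** Pressure is partly a consequence of stiffness, so adjusting may remove real difference. This stands, and it is why neither result should be ranked as the true one.

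**Conclusion.** The concern holds in a limited form. As written, the article would let a pressure difference between groups, or a pressure change over follow-up, be reported as a difference in arterial stiffness. How far that would happen is unknown: none if mean pressures are equal, and about 6% to 11% of baPWV for 10 mmHg under the assumed exponential relation.

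The conclusion rests on the pressure dependence of pulse wave velocity, which is general physiology, and on a pressure difference being plausible between people with a recent stroke and controls without one. A reader might extend the point to the trial's main result, but it concerns baPWV, a secondary outcome, and nothing shown here bears on rAIx. The change is worth making because it is cheap and protects the interpretation of the vessel outcome.

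**What to change.** 1. In the between-group and over-time baPWV models, add an analysis with the arm blood pressure taken closest to the baPWV measurement as a covariate, using the arm systolic pressure from the ankle-brachial index or the recorded vital signs.
2. Report it beside the unadjusted result, without ranking one above the other.
3. Describe a baPWV difference as a stiffness difference only where the two agree; otherwise say it cannot be separated from blood pressure.

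**Cost.** One covariate and one additional reported result per comparison. The downside is that adjustment may remove some true stiffness difference, which reporting both makes visible. Whether pressure is available at the same visits as baPWV should be confirmed against the visit schedule (Table 3), whose content is not shown. If an existing analysis plan already does this, a sentence saying so settles the point.
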